## Abstract

**Background:**

Pressure support ventilation (PSV) is one of the most frequently used ventilator modes in the intensive care unit (ICU). The successful implementation of PSV depends on matching the patient’s inspiratory effort with the ventilator support. In clinical practice, the pressure support level is usually set and adjusted according to tidal volume and respiratory rate. However, these parameters may not fully represent the patient’s effort. Previous studies have shown that pressure muscle index (PMI), which is measured as the difference between the peak and plateau airway pressure during an end-inspiratory airway occlusion, could reliably determine the low and high inspiratory effort during PSV. Herein we present the study protocol for the Inspiratory effort-Targeted Pressure Support Ventilation (IT-PSV) trial to determine the effect of a PMI-targeted pressure support setting strategy on clinical outcomes in patients undergoing PSV.

**Methods and analysis:**

This is a cluster randomized controlled trial. Sixteen ICUs in academic hospitals will be included, eight of which will be randomly allocated to the PMI-targeted group and eight to the tidal volume/respiratory rate-targeted group. Before the initiation of the study, a four-week comprehensive training program, which includes courses of PSV initiation, pressure support adjustment, and weaning process, will be conducted for all staff in the participating ICUs. Adult patients with acute hypoxic respiratory failure and undergoing PSV within 24 h will be included. Pressure support setting and adjustment will follow the strategy according to the grouping. The primary outcome is the ventilator-free days at 28 days after enrollment. The patients will be followed up until successful weaning or separation of mechanical ventilation, death, hospital discharge, or until 28 days after randomization, whichever comes first.

**Discussion:**

The IT-PSV trial will examine the effect of an inspiratory effort-targeted PSV setting strategy on the duration of mechanical ventilation. If positive, it will provide a new physiological-based PSV management that could potentially facilitate protective assisted ventilation.

**Clinical trial registration:**

ClinicalTrials.gov, identifier NCT06526598.

## Introduction

1

Mechanical ventilation is a necessary supportive care in the intensive care unit (ICU). Compared to controlled ventilator modes, assisted ventilation, during which the patient’s spontaneous breathing is maintained, can improve gas exchange and lung function, redistribute ventilation and end-expiratory volume to dependent lung areas, and prevent respiratory muscle atrophy (1). An international prospective cohort study demonstrated that the use of assisted ventilation had increased over the past two decades, and pressure support ventilation (PSV) had become the most frequently used assisted mode (2). However, preserving spontaneous breathing during positive pressure ventilation is not without safety concerns (3, 4). Under mechanical ventilation, against positive airway and alveolar pressure, vigorous inspiratory effort, especially in patients with acute lung injury, may dramatically increase global and regional lung stress and strain (3, 4). This is considered the primary mechanism of the patient’s self-inflicted lung injury (5). On the contrary, excessive support and/or deep sedation may result in low effort, which may lead to disuse atrophy of the inspiratory muscles, thereby prolonging the duration of mechanical ventilation (6). Therefore, monitoring and controlling inspiratory effort during assisted ventilation is of important clinical significance.

Although initially designed as a ventilator mode for the weaning process, PSV is widely used to assist ventilation during the acute phase of critical illness (2, 7). During PSV, the ventilator provides a constant level of pressure for breaths, which are all triggered by the patient (8). The successful implementation of PSV depends on matching the patient’s inspiratory effort with the ventilator support (7). Although esophageal pressure is used as a reference standard for inspiratory effort assessment (9, 10), its routine application is limited by the requirement of special equipment and complex computation processes (11, 12). In clinical practice, pressure support levels are usually set and adjusted according to tidal volume (VT) and respiratory rate (RR); however, these parameters may not fully represent the patient’s effort (7). Previous studies have also shown that over-assistance under PSV is not uncommon based on this setting strategy (13, 14). An easily accessible instrument is required to target the support level with the patient’s inspiratory effort at the bedside.

During PSV, an end-inspiratory airway occlusion can induce a plateau airway pressure (Paw). The difference between the peak and plateau Paw was named as pressure muscle index (PMI) (15). Studies have shown that PMI is closely correlated with inspiratory effort determined by esophageal pressure-derived indices (15–17) and electromyography of respiratory muscles (18). Our previous study also found that PMI could reliably discriminate low and high inspiratory effort with respective cutoff values of 0 and 2 cmH_2_O (19), and these cutoff values could be reliably used as a parameter to predict low and high contribution of patient’s effort during PSV (20). These results suggest the potential use of PMI as an effort-targeted indicator for PSV setting and adjustment. Moreover, PMI can be directly measured on the ventilator screen without additional equipment, suggesting its convenient bedside use.

With a cluster randomized controlled trial (RCT) design, the Inspiratory effort-Targeted Pressure Support Ventilation (IT-PSV) trial will determine the effect of a PMI-targeted pressure support setting strategy on clinical outcomes in patients undergoing PSV. We are proposing a physiological-oriented assisted ventilation management that, if found effective, could potentially change the clinical practice of mechanical ventilation.

## Methods and analysis

2

### Study design, settings, and ethics

2.1

IT-PSV is a cluster RCT that will test the influence of a PMI-targeted pressure support adjustment strategy on clinical outcomes in patients undergoing PSV. The flowchart of the trial is shown in Figure 1A.

### Randomization

2.2

The randomization will be performed by a statistician who will not be involved in the study procedures. To improve power and balance, the 16 participating ICUs (clusters) are matched in pairs with a similar number of beds and volume of patients undergoing mechanical ventilation (22). The ICUs are randomized within the pairs with a 1:1 ratio to either the PMI-targeted (*n* = 8) or VT/RR-targeted (*n* = 8) group.

Due to the nature of the intervention and control, it is not possible to blind participating ICUs, personnel providing patient care in the ICU, and researchers performing data collection. However, the researchers who conduct the statistical analyses will be blinded to the grouping.

### Patients

2.3

Mechanically ventilated patients admitted to the ICU with acute hypoxic respiratory failure (AHRF) (23) will be consecutively screened daily at 08:00–10:00 morning rounds. Patients undergoing PSV are eligible for inclusion.

#### Inclusion criteria

2.3.1

PSV initiated during the last 24 h, whether transition from controlled modes or primary initiation;Mechanical ventilation expected to be required for at least 24–48 h by responsible physicians;The partial pressure of oxygen in arterial blood (PaO_2_)/inspired oxygen fraction (FiO_2_) ≤ 300 mmHg (measuring at clinical FiO_2_ and positive end-expiratory pressure [PEEP]);No sedation or stable sedation with Richmond Agitation Sedation Scale (RASS) of −2 to +1 or Riker’s Sedation-Agitation Scale (SAS) of 3 to 4 (24).

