#### Exclusion criteria

2.3.2

Age younger than 18 years old;Initiation of PSV before ICU admission;Duration of mechanical ventilation longer than 7 days before enrollment;History of neuromuscular diseases;Clinical suspicion of increased intracranial pressure;Presentation with pneumothorax and/or bronchopleural fistula;Extracorporeal support;Moribund conditions;Refusal by the ICU physicians or the patient.

The patients will be enrolled only once during the same hospitalization. Written informed consent will be obtained from the patient or their legal representative.

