#### Data collected at the study entry

2.5.1

At baseline, demographics, comorbidities, diagnosis for ICU admission, recent medical history, reasons for mechanical ventilation, duration of ventilation before enrolment, conditions of gas exchange, and mechanical ventilation settings will be documented, as will the Acute Physiological and Chronic Health Evaluation II (APACHE II) score at the ICU admission.

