#### Primary outcome

2.6.1

The primary outcome is the ventilator-free days (VFDs) at day 28 after enrollment. The calculation of VFDs will follow the standard recommendations (30, 31).

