#### Sample size estimation

2.9.1

Our previous studies showed that the mean (± standard deviation) VFDs in Chinese academic hospitals was 19 ± 3.3 days (19, 20). An individual RCT will require 342 patients to detect a one-day increase in VFDs with a type I error (Alpha) of 0.05 and a power of 80%. According to previous studies, an intra-cluster correlation coefficient of 0.03 is used to calculate the sample size for the cluster RCT (33, 34), which results in a target of 551 recruited patients. Accounting for 15% of immeasurable PMI during PSV (19, 20), a sample of 648 will be the target, with an approximate average recruiting 40 patients in 16 participating ICUs.

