#### Statistical analysis plan

2.9.2

All statistical analyses will be conducted in accordance with the intention-to-treat principle. That is, all randomized patients will be analyzed in the groups to which they were originally allocated. Researchers performing statistical analysis will be blinded to the cluster grouping.

Categorical variables will be presented as numbers and percentages and compared using the chi-squared test or Fisher’s exact test. For continuous variables, normal distribution will be checked by Kolmogorov–Smirnov Test, and presented as mean and standard deviation or median and interquartile range, as appropriate. Comparison of continuous variables will be performed by Student’s *t*-test for normally distributed variables and the Mann–Whitney U test for non-normally distributed variables.

Time-to-event variables will be analyzed using survival analysis, and the difference between groups will be assessed with the log-rank test.

The patients will be stratified *a priori* into subgroups with:

high versus intermediate and low respiratory drive according to the P0.1 criteria reported by a previous study (29);diagnosis of acute respiratory distress syndrome (ARDS) versus non-ARDS according to the Global definition (35);long versus short duration of controlled ventilation before enrollment according to the median obtained in all enrolled patients.

Statistical analyses will be performed using MedCalc (2022 MedCalc Software Ltd., Belgium). A *p* value of less than 0.05 is considered statistically significant.

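### Patients are enrolled after the ICU knows its arm and partly on clinical judgement, but the stated VFD comparison is unadjusted, so measured case-mix differences pass into the result; their size and direction are unknown

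*Protocol article*

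**What the plan says.** All references are to the protocol article.

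- **Order of events.** Section 2.7 places the four-week training after randomisation and before the trial starts, in separate courses for each arm. Staff therefore know their arm before the first enrolment.
- **Blinding.** Section 2.2 states that "it is not possible to blind participating ICUs, personnel providing patient care in the ICU, and researchers performing data collection". Only the analysts are blinded.
- **Judgement at entry.** Section 2.3.1 requires "Mechanical ventilation expected to be required for at least 24–48 h by responsible physicians". Section 2.3.2 excludes moribund patients and lists "Refusal by the ICU physicians or the patient". Entry also requires recently started pressure support ventilation (PSV), and section 2.4.2 makes the move to PSV a recommendation to the responsible physician.
- **Safeguards.** Section 2.3 provides consecutive daily screening. Section 2.3.1 sets limits on PaO2/FiO2 and sedation score. Section 2.4.2 gives written transition criteria for both arms, and section 2.7 provides monthly audits.
- **Matching.** Section 2.2 pairs ICUs on number of beds and volume of ventilated patients.
- **Outcome and analysis.** Section 2.6.1: "The primary outcome is the ventilator-free days (VFDs) at day 28 after enrollment". Section 2.9.2 compares continuous variables with "Student’s *t*-test for normally distributed variables", or Mann-Whitney otherwise. It names no covariate.
- **Baseline data.** Section 2.5.1 collects demographics, admission diagnosis, reason for ventilation and APACHE II at ICU admission. It adds that "duration of ventilation before enrolment, conditions of gas exchange, and mechanical ventilation settings will be documented".

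**The concern.** Randomising ICUs balances the ICUs in expectation. It does not balance the patients recruited afterwards by people who know the arm. If the forecast of ventilation time, the moribund judgement, physician refusal or the timing of PSV is applied even slightly differently in the two arms, the enrolled patients differ in prognosis before treatment has any effect. Eight ICUs per arm also leave room for chance differences in severity, which the matching factors do not address.

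The target effect is one day, or 1/3.3 = 0.30 SD, so a fairly small prognostic difference matters. The stated test passes any such difference into the estimate, although prognostic variables that could remove the measured part are already collected.

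**Working it through.** **1. The plan's own figures.** Section 2.9.1 gives "VFDs in Chinese academic hospitals was 19 ± 3.3 days" and "An individual RCT will require 342 patients to detect a one-day increase in VFDs", with alpha 0.05, power 80% and ICC 0.03.
- Per arm: 2 × (1.96 + 0.842)² × 3.3² / 1² ≈ 171, so 342 in total. This reproduces.
- Clustering: 342 × [1 + (342/16 − 1) × 0.03] = 551. This reproduces.
- Immeasurable PMI: 551 / 0.85 = 648. This reproduces, at 648/16 = 40.5 patients per ICU.

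The mean of 19 and SD of 3.3 are used below.

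**2. Smallest significant difference (N = 648, normal approximation).**
- Stated unclustered test: SE = 3.3 × √(4/648) = 0.259; × 1.96 = 0.51 day.
- Cluster-aware: design effect 1 + 39.5 × 0.03 = 2.185; SE = 0.259 × √2.185 = 0.383; × 1.96 = 0.75 day.
- With 551 analysed, the two figures are 0.55 and 0.78 day.

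**3. Upper bound from omitting zero-VFD patients.** With mean 19 and SD 3.3, the share p at zero is largest when everyone else has the same value. Then p/(1 − p) = 3.3²/19² = 10.89/361, so p = 2.9%. Omitting all of them from one arm moves its mean to 19/(1 − 0.0293) = 19.57, a shift of at most 0.57 day.

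**4. Omitting the worst-prognosis patients.** Let one arm leave out the fraction q with the worst forecast, and let rho be the assumed correlation of that forecast with VFDs. On a normal model, shift = rho × 3.3 × φ(z_q)/(1 − q).

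| rho (assumed) | q for 1 day | q for 0.51 day |
|---|---|---|
| 1 | 17% | 8% |
| 0.7 | 26% | 12% |
| 0.5 | 38% | 17% |
| 0.3 | 62% | 31% |

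**5. Difference in case mix.** Bias = excess share of a patient type × its VFD gap. One day needs 20% at a gap of 5 days and 10% at a gap of 10. Patients off the ventilator in one to two days (about 26–27 VFDs, 7–8 above the mean) would need a 12.5–14% difference in share. The document gives none of these gaps or shares.

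**6. Effect on the test when there is no true effect.**

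| Selection bias (days) | p < 0.05, stated test | p < 0.05, cluster-aware |
|---|---|---|
| 0 | 18.5% | 5% |
| 0.25 | 27% | 10% |
| 0.5 | 50% | 26% |
| 1.0 | 90% | 74% |

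The 18.5% in the first row comes from ignoring clustering, which is a separate issue. The rise down each column is due to selection.

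**7. Precision from adjustment.** Relative to total variance, a cluster mean has patient-level variance 0.97/40.5 = 0.024 and between-ICU variance 0.030, so the patient-level part is 0.024/0.054 = 44%. If covariates explain an assumed 10–20% of that part only, total variance falls by 4–9% and the SE by about 2–5%.

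**The case against.** **Safeguards.** Consecutive screening, objective limits, written transition criteria, common care apart from pressure support adjustment, and audits all limit discretion. This stands. The risk is reduced, although none of these measures conceals the arm.

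**Size.** A reader might infer that slight selection could create the whole target effect: drop 5% of patients with zero VFDs from one arm and the mean goes from 19 to 19/0.95 = 20. The plan's figures rule this out. A 5% share at zero with the rest averaging 20 has variance of at least 0.05 × 19² + 0.95 × 1² = 19.0, an SD of at least 4.36 against the stated 3.3. It would also need physicians to identify those patients with certainty.

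**Direction.** A reader might also infer that the bias favours the intervention, or that the separate courses teach PSV initiation differently. The document shows neither, and section 2.4.2 sets one list of transition criteria for both arms.

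**Remedy.** Adjustment cannot remove selection on unrecorded bedside judgement. This stands. Some baseline variables are also doubtful covariates: section 2.6.2 lists ventilation time before enrolment as a secondary outcome, and arm-specific practice in starting PSV could alter it. This also stands and limits the choice of covariates.

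**Chance imbalance.** It is not bias, and a cluster-aware variance covers it. That is correct, but the stated test is not cluster-aware, and prespecified adjustment still removes the measured part.

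**Unseen analysis plan.** The tests are written into section 2.9.2, so the point concerns what is stated. Screening counts are reporting detail that a fuller document may cover, and the finding does not depend on them.

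**Conclusion.** The point holds in a limited form. Patients are recruited by staff who know the arm, partly on judgement, and the stated primary comparison makes no use of the prognostic data collected. Measured case-mix differences therefore pass into the VFD difference.

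The document does not show that selection will occur, which arm it would favour or how large it would be. At the planned mean and SD, omitting zero-VFD patients can shift an arm by at most 0.57 day. A full day needs substantial selection: 17–38% of the worst-prognosis patients at rho 1 to 0.5, and more if physicians forecast less well. A shift of about 0.5 day is at the threshold of significance for the stated test but below the 0.75 day for a cluster-aware one.

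These figures rest on the stated SD of 3.3, a normal model for the truncation results, and assumed values of rho and VFD gaps. A larger true SD would allow larger shifts. The change is worth making because covariates chosen after an imbalance has been seen carry little credibility.

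**What to change.** - **Primary model.** In a cluster-aware model for VFDs, adjust for prespecified prognostic covariates already collected that allocation is unlikely to affect: age, APACHE II at ICU admission, and main diagnosis or reason for ventilation. Give the unadjusted cluster-aware estimate as supportive.
- **Sensitivity analysis only.** Add PaO2/FiO2 at enrolment, ARDS status and ventilation time before enrolment here. They can reflect care given after the ICU knew its arm, and the last is a listed secondary outcome.
- **Limitation.** State that adjustment removes only measured imbalance.
- **Recruitment counts.** From the existing daily screening, report numbers screened, eligible, refused and enrolled by arm and ICU, so that readers can judge differential recruitment.

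The cost is a few lines of analysis text, a little more modelling and some tabulation. Treatment and sample size do not change. The precision gain is small (SE about 2–5% lower on the assumption above), so the main reason for the change is protection against measured imbalance.

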#### Exclusion criteria

2.3.2

Age younger than 18 years old;Initiation of PSV before ICU admission;Duration of mechanical ventilation longer than 7 days before enrollment;History of neuromuscular diseases;Clinical suspicion of increased intracranial pressure;Presentation with pneumothorax and/or bronchopleural fistula;Extracorporeal support;Moribund conditions;Refusal by the ICU physicians or the patient.

The patients will be enrolled only once during the same hospitalization. Written informed consent will be obtained from the patient or their legal representative.

### Study procedures

2.4

In both PMI-targeted and VT/RR-targeted groups, standard clinical care for mechanical ventilation is followed according to local routine practice, which is formatted based on international clinical guidelines, except for pressure support adjustment during PSV.

#### General standard of care for mechanical ventilation

2.4.1

Analgesia is routinely used in mechanically ventilated patients with continuous infusion of fentanyl or remifentanil. Sedation with midazolam, propofol, or dexmedetomidine is used when the patient exhibits agitation and a light sedation level is maintained on RASS of −2 to +1 or Riker’s SAS of 3 to 4 (24).

In patients with AHRF, mechanical ventilation is usually initiated on protective control ventilation, such as volume or pressure control mode, with VT 6–8 mL/kg predicted body weight (PBW), RR to control arterial partial pressure of carbon dioxide (PaCO_2_) and pH, and FiO_2_ and PEEP to maintain pulse arterial oxygen saturation (SpO_2_) between 90 and 95% (25, 26).

#### Transition of control modes to PSV

2.4.2

During the morning rounds, the responsible ICU physicians check the ventilator mode for each patient. The ventilator mode is recommended to transit from controlled modes to PSV if all the following criteria are met:

The patient is able to trigger ventilator breaths;PaO_2_/FiO_2_ above 100 mmHg;PEEP below 15 cmH_2_O;Stable hemodynamic status (none or stable doses of vasopressors);No sedation or light sedation ([RASS] of −2 to +1 or [SAS] of 3 to 4).

#### PSV setting strategy

2.4.3

In both the PMI-targeted and VT/RR-targeted groups, the same principle PSV settings are followed except for the adjustment of pressure support level:

The inspiratory trigger sensitivity is set as 1–2 L/min for the flow-trigger or 1.5–3 cmH_2_O for the pressure-trigger;Inspiration-to-expiration cycle-off is set as 25% of the peak inspiratory flow. Responsible physicians can adjust this parameter in case of suspected cycle-off patient-ventilator asynchrony;FiO_2_ and PEEP are set to maintain SpO_2_ between 90 and 95%. Specifically, if SpO_2_ is lower than 90%, PEEP and then FiO_2_ will be increased by 2 cmH_2_O and 0.1, respectively; whereas if SpO_2_ is higher than 95%, FiO_2_ and then PEEP will be decreased by 0.1 and 2 cmH_2_O, respectively.

In the VT/RR-targeted group, the pressure support is adjusted to obtain a VT between 6 and 8 mL/kg PBW, RR between 20 and 35 breaths/min, and no signs of respiratory distress, such as prominent use of the accessory respiratory muscles, nose flaring, retractions, etc. (Figure 2A).

**Figure 2 fig2:**
[figure not shown]
Pressure support setting and adjustment strategy in VT/RR-targeted group **(A)** and PMI-targeted group **(B)**. PBW, predicted body weight; PMI, pressure muscle index; RR, respiratory rate; VT, tidal volume.

In the PMI-targeted group, the pressure support is adjusted according to the algorithm shown in Figure 2B. During PSV, after an end-inspiratory airway occlusion, Paw will reach a plateau. PMI can be measured on the ventilator screen as plateau Paw minus peak Paw by using a sliding marking line when the screen frozen function is initiated. According to our previous studies, a PMI value of 0 to 2 cmH_2_O will be used as the target for pressure support adjustment. This PMI range represents a well-accepted normal inspiratory effort (19, 20).

During the study period in the two groups, pressure support adjustment will be performed at least twice daily.

